## Abstract

**Background:**

Although the risk of developing colorectal cancer (CRC) is 2-4 times higher in case of a positive family history, risk-adapted screening programs for family members related to CRC- patients do not exist in the German health care system. CRC screening recommendations for persons under 55 years of age that have a family predisposition have been published in several guidelines.

The primary aim of this study is to determine the frequency of positive family history of CRC (1^st^ degree relatives with CRC) among 40–54 year old persons in a general practitioner (GP) setting in Germany. Secondary aims are to detect the frequency of occurrence of colorectal neoplasms (CRC and advanced adenomas) in 1^st^ degree relatives of CRC patients and to identify the variables (*e.g.* demographic, genetic, epigenetic and proteomic characteristics) that are associated with it. This study also explores whether evidence-based information contributes to informed decisions and how screening participation correlates with anxiety and (anticipated) regret.

**Methods/Design:**

Prior to the beginning of the study, the GP team (GP and one health care assistant) in around 50 practices will be trained, and about 8,750 persons that are registered with them will be asked to complete the “Network against colorectal cancer” questionnaire. The 10 % who are expected to have a positive family history will then be invited to give their informed consent to participate in the study. All individuals with positive family history will be provided with evidence-based information and prevention strategies. We plan to examine each participant’s family history of CRC in detail and to collect information on further variables (*e.g.* demographics) associated with increased risk. Additional stool and blood samples will be collected from study-participants who decide to undergo a colonoscopy (*n* ~ 350) and then analyzed at the German Cancer Research Center (DKFZ) Heidelberg to see whether further relevant variables are associated with an increased risk of CRC. One screening list and four questionnaires will be used to collect the data, and a detailed statistical analysis plan will be provided before the database is closed (expected to be June 30, 2015).

**Discussion:**

It is anticipated that when persons with a family history of colorectal cancer have been provided with professional advice by the practice team, there will be an increase in the availability of valid information on the frequency of affected individuals and an increase in the number of persons making informed decisions. We also expect to identify further variables that are associated with colorectal cancer. This study therefore has translational relevance from lab to practice.

**Trial registration:**

German Clinical Trials Register DRKS00006277

**Electronic supplementary material:**

The online version of this article (doi:10.1186/s12885-015-1600-7) contains supplementary material, which is available to authorized users.

## Background

The risk of developing colorectal cancer (CRC) is 2–4 times higher in case of a family predisposition [1, 2]. A repeat occurrence within a family can be noted in around 30 % of all cases of CRC, whereby around 5 % of these are associated with hereditary types of CRC. The family predisposition for the remaining ~25 % of cases has not yet been properly explained [3]. The different constellations of risk are currently not taken into account in the directives of the German Federal Joint Committee on cancer screening [4]. In 2013, the usefulness of colorectal cancer screening for persons under 55 years of age with a family predisposition was declared by the IQWIG to be uncertain, as no high quality studies could be identified in which comprehensive screening strategies in the general population had been analyzed using anamnestic instruments [5]. The “Network against colorectal cancer” questionnaire has shown that information on a positive family history is partly overstated when patients fill in questionnaires themselves, as opposed to when they are personally interviewed, and that when findings are positive, only 40 % of those concerned inform their GP or gastroenterologist [6]. In two current reviews, the role of the GP and other medical personnel is described as being the most important factor influencing the decision to participate in screening examinations [7, 8], and as having a greater influence than written invitations [8]. As around 92 % of the German general population have a GP [9] and around 89 % annually make use of outpatient services [10], screening participation rates are expected to be high. The “European Guideline for Quality Assurance in CRC screening and diagnosis” recommends that patients should be spoken to personally [11]. This is easy for the GP to do on account of the trusting relationship he has with his patients.

In view of the new law on the further development of cancer screening, as well as further clarification demanded by the German Federal Joint Committee, the proposed project could raise the awareness of the importance of family predisposition for future CRC screening programs [12].

## Methods/Design

### Research questions

The following primary research question will be addressed:What is the frequency of positive family history of CRC (1^st^ degree relatives with CRC) among 40–54 year old persons in a German GP setting?

Secondary research questions are:What is the frequency of colorectal neoplasms (CRC and advanced adenomas) in 1^st^ degree relatives of CRC patients in a German GP setting?What variables (e.g., demographic, genetic, epigenetic and proteomic characteristics) are associated with an increased risk of CRC?How can evidence-based information contribute to informed decisions with respect to screening?How does screening participation correlate with anxiety and regret?

### Study design and setting

FRIDA.Frankfurt is a cross-sectional study in a general practice setting. Prior to the beginning of the study, the practice team (GP and one health care assistant (HCA)) will be briefly trained by study personnel in how to conduct the study in their practices. Before this session, a list of all 40–54 year old patients who have attended the practice within the last twelve months will be compiled by means of the practice software. Afterwards the HCA will contact eligible patients and complete the “Network against colorectal cancer” questionnaire [13] (see screening list, Additional file 1) during a routine practice visit, or per telephone.

Those who have a positive family history will then be invited to participate in the study and to give their informed consent to do so. With the help of study materials that are presented clearly and informatively (both graphic and text based), the GP is expected to be able to provide family members related to CRC patients with adequate evidence-based information and to describe prevention strategies. During this *first practice visit* we plan to examine the participant’s family history of (colorectal-) cancer in further detail, collect information on previous CRC-screening tests, and gather information on other variables (e.g. demographics) associated with an increased risk of CRC (see questionnaire 1, Additional file 2). Study participants with a hereditary risk of CRC (suspected or already known) will be documented and excluded from subsequent study-phases.

In a *second practice visit* within two weeks of the first, details on anxiety, anticipated regret and reasons for or against participation with respect to screening will be collected before the study participants inform their GP about their decision. Furthermore, informed decision will be assessed using the validated instrument from Steckelberg et al. [14]. The selected screening test (colonoscopy, fecal occult blood test) will be documented (see questionnaire 2, Additional file 3).

If study participants are willing to undergo a colonoscopy, the GP will schedule an appointment with the gastroenterologist, and ask the participant for a blood- and stool-sample and to fill in an additional questionnaire (see questionnaire 3, Additional file 4). The results of the colonoscopy will be documented from the gastroenterologist’s report for the GP. We will also collect information on study participants who are not willing to participate in CRC-screening (e.g. colonoscopy before study participation due to a known positive family history of CRC).

*Twelve weeks after the first practice visit,* questionnaires asking about anxiety and regret will be sent out by post to all persons who participate in the study (see questionnaire 4, Additional file 5). For further details see flow chart (Fig. 1).

**Fig. 1 Fig1:**
[figure not shown]
Flow chart of the FRIDA.Frankfurt Study

Details on methods and design are laid down in the original study protocol, which can be provided by the corresponding author on demand.

### Main practice and patient in- and exclusion criteria

Doctors at participating trial sites must work as a general practitioner (GP or specialist in internal medicine), provide health services to persons with German statutory health insurance, have software which is capable of detecting potentially eligible patients, and work in a practice located in the German state of Hesse. Participating GPs and Health Care Assistants must also agree to the contractual obligations of the trial.

Patients must be 40–54 years of age, regularly attend the GP’s practice (at least one contact in the last 12 months) and sign an informed consent form. A lack of German language skills and gravidity are exclusion criteria for patients.

### Sample size calculation

As of August 2013, the “Forschungsnetzwerk Allgemeinmedizin Frankfurt” (ForN) [15] database contained approximately 100 general practices. An average-sized practice treats about 1000 patients/quarter of which about 25 % are 40–54 years of age. Over the course of a year, about 250 eligible patients will attend any one practice. It is to be expected that at least 50 % of practices (50) will participate in the study and at least 70 % of patients will complete the questionnaire (175/practice). The expected sample size is at least 8,750 of which about 875 (10 %) are expected to have a positive family history of colorectal cancer [16]. Of these, we expect around 350 (40 %) persons to follow the invitation to have a colonoscopy.

### Recruitment, study timeline and reimbursement

The trial will be primarily conducted in general practices in the state of Hesse. Eligible practices will be recruited mainly through the “Forschungsnetzwerk Allgemeinmedizin Frankfurt” (ForN) which is a network of general practices that have successfully conducted research projects with our Institute [15]. During an approximately eight-month period beginning in September, 2014, about 8,750 persons attending the general practices will be asked about their family history (see Fig. 2). As compensation, recruitment practices will receive €2 per individual that is interviewed by the HCA on the basis of the “network against colorectal cancer questionnaire” / screening list, and €10 per individual that is counselled by a GP, provided with the evidence-based decision aid, and completed all questionnaires on risk-factors, anxiety, (anticipated) regret and informed decision.

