### Data collection and quality assurance/avoidance of biases and monitoring

At the practices, the HCA will contact eligible patients and complete the “Network against colorectal cancer” questionnaire in a screening list with them (see screening list, Additional file 1). Every document includes information on how to fill in the form. The informed consent forms are sent to the Institute of General Practice (IGP) via fax on the day of the participant’s visit to the practice, and the questionnaires will later be collected from the practice by a member of the study team. Questionnaire 4 will be send to the study-participants by post. If necessary, the IGP will send out a reminder to participants after 2 weeks. All questionnaires are shown in Additional files 2, 3, 4 and 5.

The IGP study team will ensure that all processes in the trial comply with Good Clinical Practice (GCP) guidelines, the legal requirements and the standard operating procedures (SOPs) of the IGP. The patient questionnaires, patient information brochure and informed consent form will be piloted to check their comprehensibility and applicability. During the first visit, participating GPs and the HCA will be thoroughly trained and provided with the information required to conduct all steps in the study. Amongst other things, this will include the identification of suitable patients, help for patients in filling out the questionnaire on socio-demographic data, and the collection of data on those that are not willing to participate.

All information from forms (e.g. CRFs) will be transferred to the clinical study database (IBM SPSS Statistics). A data check of this database will take place according to pre-defined trial rules (range-, validity-, and consistency- checks according to defined SOPs developed during the course of the trial and documented in the trial master file). Follow-up enquiries resulting from the data plausibility check will be resolved with the help of the GP or HCA concerned.

The collection and processing of patient data will always be conducted using the patient identification number (Pat.-ID) pseudonym from the GP’s practice software. To ensure high-quality data, all pseudonymization will be conducted by the trained HCA in the GP’s practice.

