For the future investigation of genetic, epigenetic and proteomic biomarkers associated with CRC-risk, a blood and stool sample will be taken from study-participants that have decided to undergo a colonoscopy. The blood and stool samples and data from questionnaires about other risk-factors will be transferred to the German Cancer Research Center (DKFZ) in pseudonymized form and stored there. In addition, a qualitative and a quantitative fecal occult blood test will be performed at the DKFZ. All blood and stool samples, as well as further data, will be anonymized at the DKFZ and stored in the central biorepository.

Study members of the IGP will perform on-site monitoring visits as frequently as necessary and record the dates of their visits in a database (Access®). At the visits, a study member will check the completeness and accuracy of the data, and, if necessary, compare the data entered into the CRFs with clinical records (source documents). Direct access to source documents must be permitted in order to verify that the data recorded in the CRF and other forms are consistent with the original source data. Findings from this review will be discussed with the GP and HCA. The study members will stay in regular contact with the GP and HCA and provide feedback on the course of the study.

Data collection is scheduled to be completed by June 30, 2015.

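### Eight months of screening from September 2014 plus the 12-week Questionnaire 4 and its reminder does not fit within the June 30, 2015 end of data collection

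*Protocol article*

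**What the plan says.** The section on recruitment, study timeline and reimbursement fixes the screening period: "During an approximately eight-month period beginning in September, 2014, about 8,750 persons attending the general practices will be asked about their family history".

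The section on study design and setting places the first practice visit after a positive screening result. It then sets a postal follow-up, Questionnaire 4. Its timing is given as "Twelve weeks after the first practice visit". Its content and recipients are given in these words: "questionnaires asking about anxiety and regret will be sent out by post to all persons who participate in the study". The section on data collection and quality assurance adds: "If necessary, the IGP will send out a reminder to participants after 2 weeks".

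The same section gives the end date: "Data collection is scheduled to be completed by June 30, 2015". The abstract gives that day for database closure as well, promising the detailed analysis plan "before the database is closed (expected to be June 30, 2015").

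Nothing in the text shown stops first visits early, shortens the twelve-week interval for late entrants, or provides for questionnaires that come back after June 30. The timeline figure is not available in the text reviewed.

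**The concern.** The follow-up clock starts at each person's first practice visit, which cannot precede screening. The study therefore needs at least twelve weeks after the last first visit, plus two weeks where a reminder is sent. Eight months from any day in September 2014 ends between April 30 and May 29, 2015. That leaves one to two months before June 30, not three.

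The data at risk are the week-12 anxiety and regret responses. The second visit collects anxiety and anticipated regret. Questionnaire 4 is the only instrument described as asking about regret itself, so the secondary question on how screening participation correlates with anxiety and regret depends on it. If June 30 were enforced, these responses would be missing according to calendar date of entry. Some other participants would have Questionnaire 4 but no reminder, so response could also differ between early and late entrants for purely administrative reasons.

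**Working it through.** **The plan's own figures.** From the sample size section: 100 practices × 50% = 50 practices; 250 eligible patients × 70% = 175 per practice; 50 × 175 = 8,750 screened; 8,750 × 10% = 875 with a positive family history. These reproduce exactly.

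**Inputs from the documents.** Start in September 2014; screening for about 8 months; Questionnaire 4 at 12 weeks (84 days) after the first visit; reminder 2 weeks later (84 + 14 = 98 days); end date June 30, 2015.

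**Assumptions.** The first visit takes place on the day of screening, which is the most favourable case. Accrual is uniform over the window. All 875 consent and stay in the study, which makes the counts upper figures. The documents state none of these.

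**Step 1: latest first visit that fits.**
- Questionnaire 4 posted by closure: June 30 − 84 days = April 7, 2015.
- Reminder also sent by closure: June 30 − 98 days = March 24, 2015.

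Both dates allow no time for the questionnaire to come back.

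**Step 2: when the last items fall due.** Eight months is 242 days for each start date below. Days after June 30 are in parentheses.

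| Start | Last screening | Last Questionnaire 4 | Its reminder |
|---|---|---|---|
| Sept 1 | April 30 | July 23 (23) | Aug 6 (37) |
| Sept 15 | May 14 | Aug 6 (37) | Aug 20 (51) |
| Sept 30 | May 29 | Aug 21 (52) | Sept 4 (66) |

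**Step 3: share of the window affected.** Share = days after the latest date that fits ÷ 242; count = share × 875.

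| Start | No Questionnaire 4 point | No room for reminder |
|---|---|---|
| Sept 1 | 23/242 = 9.5%, about 83 | 37/242 = 15.3%, about 134 |
| Sept 15 | 37/242 = 15.3%, about 134 | 51/242 = 21.1%, about 184 |
| Sept 30 | 52/242 = 21.5%, about 188 | 66/242 = 27.3%, about 239 |

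**Step 4: sensitivity.**
- A 14-day gap between screening and first visit with a September 1 start raises the shares to 37/242 = 15.3% and 51/242 = 21.1%.
- Seven months from September 1 (to March 31) puts the last Questionnaire 4 on June 23, in time, but its reminder on July 7.
- Seven months from September 15 (to April 14) puts Questionnaire 4 itself on July 7.

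**Step 5: colonoscopy.** The second visit comes up to 14 days after the first, so the last one falls between May 14 (September 1 start) and June 12 (September 30 start). That leaves 47 to 18 days before June 30. No waiting time is stated, so no loss can be calculated.

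**The case against.** The strongest reply is that these dates are soft. The recruitment period is approximate, the end of collection is scheduled, and closure is expected. With a September 1 start, stopping first visits on April 7, about 7.2 months in, would let every Questionnaire 4 be posted in time. No passage says a late return would be discarded, and the timeline figure might separate screening from follow-up. This tempers the point without removing it. The rounding works only for an early September start, and it fails once the reminder or return time is counted. The written dates still need reconciling.

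It is also fair to say that late entrants do not drop out of the anxiety and regret question altogether. At the second visit, "within two weeks of the first, details on anxiety, anticipated regret and reasons for or against participation with respect to screening will be collected". What they would lose is the week-12 measure.

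A reader might go further and infer that colonoscopy results, and hence the frequency of neoplasms, would be selectively lost. The documents do not support that. They say only that "the GP will schedule an appointment with the gastroenterologist", with no interval or deadline, and 18 to 47 days remain after the last second visit.

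A reader might also infer that keeping June 30 means a smaller sample. It does not: the 8,750 is built from practices and patients per practice, not from months of accrual, and screening can continue after the last first visit that still allows Questionnaire 4.

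**Conclusion.** The stated schedule is internally inconsistent. For any September 2014 start, eight months plus twelve weeks ends between July 23 and August 21, 2015, which is 23 to 52 days after the stated end of data collection. The reminder runs 37 to 66 days past it.

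If June 30 were enforced, about 9.5% to 21.5% of the window would have no Questionnaire 4 point and 15.3% to 27.3% no room for a reminder: at most about 83 to 188 and 134 to 239 of 875. The shares rest on uniform accrual and a first visit on the day of screening; a gap before the first visit, or time for return, would raise them. The reminder figures matter only for those who would need one. If June 30 were not enforced, no data need be lost, but the stated closure date would be wrong.

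The effect is confined to the week-12 part of one secondary question. The primary outcome comes from the screening list and is untouched, as are the second-visit measures. Severity is moderate to minor.

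**What to change.** Reconcile the abstract, the recruitment timeline, the study design section and the data collection section. Set the end of data collection and database closure to the last first-visit date + 12 weeks + the 2-week reminder + a stated return time. Counting from the last reminder (August 6 to September 4) and assuming about 25 days for return, this gives roughly the end of August to the end of September 2015. The analysis plan is tied to closure, so its deadline moves with it.

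If June 30 must stay, state a last first-visit date for Questionnaire 4 follow-up: about March 24, 2015 to fit the reminder, and earlier if return time is to fit too. Screening for the primary outcome can continue after that date, and the 8,750 need not be lowered. The report should then say that the week-12 analysis covers first visits up to that date.

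The first option costs a date change and closure two to three months later. The second costs the week-12 data of later entrants, by a declared rule. Neither adds patients or procedures.

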**Fig. 2 Fig2:**
[figure not shown]
Timeline of the of the FRIDA.Frankfurt Study

### Data collection and quality assurance/avoidance of biases and monitoring

At the practices, the HCA will contact eligible patients and complete the “Network against colorectal cancer” questionnaire in a screening list with them (see screening list, Additional file 1). Every document includes information on how to fill in the form. The informed consent forms are sent to the Institute of General Practice (IGP) via fax on the day of the participant’s visit to the practice, and the questionnaires will later be collected from the practice by a member of the study team. Questionnaire 4 will be send to the study-participants by post. If necessary, the IGP will send out a reminder to participants after 2 weeks. All questionnaires are shown in Additional files 2, 3, 4 and 5.

The IGP study team will ensure that all processes in the trial comply with Good Clinical Practice (GCP) guidelines, the legal requirements and the standard operating procedures (SOPs) of the IGP. The patient questionnaires, patient information brochure and informed consent form will be piloted to check their comprehensibility and applicability. During the first visit, participating GPs and the HCA will be thoroughly trained and provided with the information required to conduct all steps in the study. Amongst other things, this will include the identification of suitable patients, help for patients in filling out the questionnaire on socio-demographic data, and the collection of data on those that are not willing to participate.

All information from forms (e.g. CRFs) will be transferred to the clinical study database (IBM SPSS Statistics). A data check of this database will take place according to pre-defined trial rules (range-, validity-, and consistency- checks according to defined SOPs developed during the course of the trial and documented in the trial master file). Follow-up enquiries resulting from the data plausibility check will be resolved with the help of the GP or HCA concerned.

The collection and processing of patient data will always be conducted using the patient identification number (Pat.-ID) pseudonym from the GP’s practice software. To ensure high-quality data, all pseudonymization will be conducted by the trained HCA in the GP’s practice.

For the future investigation of genetic, epigenetic and proteomic biomarkers associated with CRC-risk, a blood and stool sample will be taken from study-participants that have decided to undergo a colonoscopy. The blood and stool samples and data from questionnaires about other risk-factors will be transferred to the German Cancer Research Center (DKFZ) in pseudonymized form and stored there. In addition, a qualitative and a quantitative fecal occult blood test will be performed at the DKFZ. All blood and stool samples, as well as further data, will be anonymized at the DKFZ and stored in the central biorepository.

Study members of the IGP will perform on-site monitoring visits as frequently as necessary and record the dates of their visits in a database (Access®). At the visits, a study member will check the completeness and accuracy of the data, and, if necessary, compare the data entered into the CRFs with clinical records (source documents). Direct access to source documents must be permitted in order to verify that the data recorded in the CRF and other forms are consistent with the original source data. Findings from this review will be discussed with the GP and HCA. The study members will stay in regular contact with the GP and HCA and provide feedback on the course of the study.

Data collection is scheduled to be completed by June 30, 2015.

